### **Questionnaire 12 months**

Q 12: Har ditt arbete varit kroppsligt aktivt den senaste månaden? *With a 6 point Likert scale (0=Inte aktuellt jag jobbar inte, 1= nej inte kroppsligt aktivt alls, 2=ja, lite kroppsligt aktivt, 3=Ja*

[figure not shown]

*måttligt kroppsligt aktivt, 4= Ja, mycket kroppsligt aktivt, 5= annat) The answers will be dichotomized with a cut-off point between 2 and 3 prior to analysis.*

*Q 219: Hur ofta har Du varit fysiskt aktivt i 30 minuter eller mer den senaste månaden..? With a 4 point Likert scale (1= aldrig, 2=ibland (1-2 ggr/v), 3=Ofta (3-4 ggr/v), 4= Dagligen eller nästan dagligen (5-7 ggr/vecka)) The answers will be dichotomized with a cut-off point between 2 and 3 prior to analysis.*

*Q 235: Hur ofta har Du varit tvungen att trycka på eller krysta för att börja kissa den senaste månaden? with a 6 point Likert scale (1=aldrig, 2=färre än 1 av 5 vattenkastningar, 3=färre än hälften av vattenkastningar, 4= ungefär hälften av vattenkastningar, 5= fler än hälften av vattenkastningar, 6=alltid). The answers will be dichotomized with a cut-off point between 3 and 4 prior to analysis. Interpreted as risk factor and included in analyses if answered "yes" on same or previous questionnaire as inguinal hernia is identified.*

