**Questionnaire 24 months**

Q 50: Have you contacted the health care due to groin hernia? (Yes/No)

Q 58: Have you contacted the health care due other reasons? (Yes/No). If yes - reason for contact.

Q 59-77: Have you been re-admitted to hospital? (Yes/No). If yes – reason for and date of re-admittance? Only applicable if date is after prostate surgery date.

Q 78-90: Have you had surgery after your prostate surgery during the past year? (Yes/No). If yes – reason and date.

If at least one of the CRF reports indicates the patient has been re-operated or at least one of the items in the questionnaire indicates a suspected hernia formation, then the outcome will be defined as the occurrence of hernia (positive outcome).

If neither the CRF nor the questionnaire reported events related to inguinal hernia formation, then the outcome will be defined as the no occurrence of hernia (negative outcome).

Missing values will be interpreted as absence of hernia

The primary endpoint is proportion of patients with at least one inguinal hernia within 24 months after surgery.

Possible preoperative risk factors for inguinal herniaThe following risk factors for developing an inguinal hernia will be evaluated:

1. Age
2. Physical workload

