**Low risk T1-2 vs high risk T3-4**

**BASELINE PATIENT CHARACTERISTICS, TUMOUR FACTORS, COMORBIDITIES AND RISK FACTORS ARE BASED UPON:**

### **Preoperative questionnaire**

Sociodemographics (Q4-6), BMI (Q8-9), relevant comorbidities (Q30, 35, 41, 43, 44), previous abdominal surgery (Q52), previous IH surgery (Q46, 47), smoking (Q57), physical activity (Q143), urinary flow (Q149)

Patients were dichotomized as current smoker (including pipe smoking) or non-smoker (former smoker or never smoker) according to their answer to the question “Do you smoke or have you smoked?”.

Q 143: Hur ofta har Du varit fysiskt aktivt i 30 minuter eller mer den senaste månaden..? *With a 4 point Likert scale (1= aldrig, 2=ibland (1-2 ggr/v), 3=Ofta (3-4 ggr/v), 4= Dagligen eller nästan dagligen (5-7 ggr/vecka)) The answers will be dichotomized with a cut-off point between 2 and 3 prior to analysis.*

Q 146: Hur ofta har Du varit tvungen att trycka på eller krysta för att börja kissa den senaste månaden? *With a 6 point Likert scale (1=aldrig, 2=färre än 1 av 5 vattenkastningar, 3=färre än hälften av vattenkastningar, 4= ungefär hälften av vattenkastningar, 5= fler än hälften av vattenkastningar, 6=alltid). The answers will be dichotomized with a cut-off point between 3 and 4 prior to analysis.*

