### **Questionnaire three months:**

Q 8: Har ditt arbete varit kroppsligt aktivt den senaste månaden? *With a 6 point Likert scale (0=Inte aktuellt jag jobbar inte, 1= nej inte kroppsligt aktivt alls, 2=ja, lite kroppsligt aktivt, 3=Ja måttligt kroppsligt aktivt, 4= Ja, mycket kroppsligt aktivt, 5= annat) The answers will be dichotomized with a cut-off point between 2 and 3 prior to analysis.*

Q 205: Hur ofta har Du varit fysiskt aktivt i 30 minuter eller mer den senaste månaden..? *With a 4 point Likert scale (1= aldrig, 2=ibland (1-2 ggr/v), 3=Ofta (3-4 ggr/v), 4= Dagligen eller nästan dagligen (5-7 ggr/vecka)) The answers will be dichotomized with a cut-off point between 2 and 3 prior to analysis.*

Q 221: Hur ofta har Du varit tvungen att trycka på eller krysta för att börja kissa den senaste månaden? *With a 6 point Likert scale (1=aldrig, 2=färre än 1 av 5 vattenkastningar, 3=färre än hälften av vattenkastningar, 4= ungefär hälften av vattenkastningar, 5= fler än hälften av vattenkastningar, 6=alltid). The answers will be dichotomized with a cut-off point between 3 and 4 prior to analysis.*

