### **Questionnaire 24 months**

*Q 23: Har ditt arbete varit kroppsligt aktivt den senaste månaden? With a 6 point Likert scale (0=Inte aktuellt jag jobbar inte, 1= nej inte kroppsligt aktivt alls, 2=ja, lite kroppsligt aktivt, 3=Ja måttligt kroppsligt aktivt, 4= Ja, mycket kroppsligt aktivt, 5= annat) The answers will be dichotomized with a cut-off point between 2 and 3 prior to analysis.*

*Q 230: Hur ofta har Du varit fysiskt aktivt i 30 minuter eller mer den senaste månaden..? With a 4 point Likert scale (1= aldrig, 2=ibland (1-2 ggr/v), 3=Ofta (3-4 ggr/v), 4= Dagligen eller nästan dagligen (5-7 ggr/vecka)) The answers will be dichotomized with a cut-off point between 2 and 3 prior to analysis.*

*Q 256: Hur ofta har Du varit tvungen att trycka på eller krysta för att börja kissa den senaste månaden? With a 6 point Likert scale (1=aldrig, 2=färre än 1 av 5 vattenkastningar, 3=färre än hälften av vattenkastningar, 4= ungefär hälften av vattenkastningar, 5= fler än hälften av vattenkastningar, 6=alltid). The answers will be dichotomized with a cut-off point between 3 and 4 prior to analysis. Interpreted as risk factor if answered "yes" on same or previous questionnaire as inguinal hernia is identified. Interpreted as risk factor and included in analyses if answered "yes" on same or previous questionnaire as inguinal hernia is identified*

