## ***Covariates, stratum and subgroups***

No additional variables apart from the variables that will be evaluated for risk factors will be included as covariates in the statistical model.

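### Postoperative straining is coded by reference to the questionnaire at which the hernia is found, so exposure depends on the outcome, and the SAP contradicts itself on whether straining enters the model

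*SAP*

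**What the plan says.** In the SAP section Variables and Endpoints, straining to start urination is asked four times: preoperatively (Q 146), at three months (Q 221), at 12 months (Q 235) and at 24 months (Q 256). Each is a six-point frequency item about the last month. For each, "The answers will be dichotomized with a cut-off point between 3 and 4 prior to analysis"; that cut is the only available meaning of a yes.

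Under Questionnaire 12 months the SAP adds: "Interpreted as risk factor and included in analyses if answered 'yes' on same or previous questionnaire as inguinal hernia is identified". Under Questionnaire 24 months the same rule, again tied to the "same or previous questionnaire as inguinal hernia is identified", appears twice in slightly different words. The preoperative and three-month straining items carry no such rule, and neither do the workload and physical activity items.

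The outcome is a single binary one: "The primary endpoint is proportion of patients with at least one inguinal hernia within 24 months after surgery". It is positive if any CRF reports a hernia operation or any questionnaire item indicates a suspected hernia. The section Statistical method fits one modified Poisson regression to it and describes no time-updated covariate.

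Straining is not among the nine numbered risk factors or the nine factors named under Statistical method. The section Covariates, stratum and subgroups states: "No additional variables apart from the variables that will be evaluated for risk factors will be included as covariates in the statistical model".

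**The concern.** A risk factor has to be defined in the same way for men who do and do not develop the outcome. Here the questionnaires that count are chosen by when the hernia was identified. A man with no hernia has no such questionnaire, and the SAP names no substitute. At the SAP's illustrative incidences of 10% and 12.5%, that is close to nine men in ten, and whoever programs the variable must invent their coding.

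The order in time is also open. Straining is asked about the last month, whereas the surgery items on the 12- and 24-month questionnaires cover the past year. Counting the same questionnaire can therefore pair a hernia with straining that started after it. In addition, a hernia reported only on a CRF has no identifying questionnaire at all, so the rule is incomplete even for some cases.

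Evaluating risk factors is the SAP's stated secondary objective, and they are estimated in the same model as the surgical comparison. If straining is entered under this rule, its reported association could be produced by the coding alone.

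**Working it through.** **The SAP's own figures.** It gives none for straining. Its only computed figures are the powers of approximately 35% and 55% under Sample size. These reproduce for two proportions with 2764 and 942 men at two-sided 5% (34.0% and 53.6% with unpooled variance; 34.8% and 54.9% with continuity correction) and do not bear on this point.

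**Does straining enter the model?**
- Questionnaire 12 months and Questionnaire 24 months: yes, it is to be included in the analyses.
- Numbered risk factors, and the list under Statistical method: not named.
- Covariates, stratum and subgroups: nothing beyond the evaluated risk factors may enter.

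These statements cannot all hold.

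**What the coding does if straining enters.**

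Inputs:
- Hernia incidence *i* from the SAP's illustration: (2764 × 0.10 + 942 × 0.125) / 3706 = 394.15 / 3706 = 0.106.
- Assumed, because the SAP gives no figure: straining prevalence 10% at every questionnaire, no true association, and either independent answers or a within-man correlation of 0.7 (beta-binomial).
- Cases are scored over two questionnaires (same or previous).

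Probability of at least one yes over *n* questionnaires:
- Independent: 1 − 0.9^n. This gives 0.100 (n = 1), 0.190 (n = 2) and 0.344 (n = 4).
- Correlation 0.7: a + b = 1/0.7 − 1 = 0.4286 and b = 0.9 × 0.4286 = 0.3857. The probability of no yes is the product of (b + k)/(a + b + k) for k = 0 to n − 1. This gives 0.100 (n = 1), 0.127 (n = 2) and 0.153 (n = 4).

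With e1 the exposed share of cases and e0 that of non-cases:

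RR = [i·e1 / (i·e1 + (1−i)·e0)] ÷ [i(1−e1) / (i(1−e1) + (1−i)(1−e0))]

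Worked example, non-cases scored over four questionnaires, independent answers: 0.106 × 0.190 / (0.106 × 0.190 + 0.894 × 0.344) = 0.0615. Among the unexposed, 0.106 × 0.810 / (0.106 × 0.810 + 0.894 × 0.656) = 0.128. The ratio is 0.48.

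| Coding of men without hernia | RR, independent | RR, correlation 0.7 |
|---|---|---|
| Yes on any of four questionnaires | 0.48 | 0.82 |
| Yes on one questionnaire | 1.91 | 1.27 |
| Yes on either of two questionnaires | 1.00 | 1.00 |
| Never exposed (literal reading) | 11.4 | 10.7 |

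In the last row every exposed man is a case, so the exposed risk is 1 and the RR is the inverse of the unexposed risk: 1/0.0876 and 1/0.0938.

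**Simulation.** N = 3706, true RR = 1, incidence 6–12.5%, prevalence 5–20%, latent correlation 0.3 or 0.6, hernias first identified at 3, 12 and 24 months in assumed shares of 20/40/40%, 300 replicates per scenario, crude RR with a nominal 5% test:
- Non-cases never exposed: median RR about 9–24, rejection 100%.
- Cases by the rule, non-cases yes on any of four: median RR 0.52–0.65, rejection 57–100%.
- Cases yes at any questionnaire up to identification, non-cases yes on any of four: median RR 0.80–0.86, rejection 10–72%.
- Preoperative answer for everyone: median RR 0.97–1.02, rejection 3–8%, which is simulation noise around 5%.

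**The case against.** The strongest reply is that straining never reaches the model. Both risk-factor lists omit it, the planned patient-characteristics summary omits it, and other covariates are barred. If those sections govern, no straining risk ratio is produced and no bias arises. This stands as a limit on the point. It does not remove it, because it relies on one half of a contradiction and the other half says in terms that straining is included.

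A second reply is that bias is not inevitable. If men without hernia are scored on two questionnaires, for example the 12- and 24-month items that carry the rule, the RR is 1.0 under the assumptions above. That also stands, but the SAP does not state this coding, the result needs equal prevalence at each questionnaire, and straining that began after the hernia would still be counted. The RR of about 11 needs the most extreme reading, in which men without hernia are unexposed whatever they answered.

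The SAP's promise of cautious interpretation softens the reporting of a false association but does not repair the variable.

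A reader might go further and infer that the RALP versus RRP estimate is contaminated, since voiding after surgery may depend on the operation. The SAP gives no source for such a dependence, and no effect on the contrast has been computed. Adjusting for a post-exposure variable is also a separate question from the hernia-linked rule.

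**Conclusion.** The point holds in conditional form. It is certain from the text that the 12- and 24-month straining rule makes exposure depend on the outcome, leaves it undefined for men without a hernia and allows straining after the hernia. It is equally certain that the SAP contradicts itself on whether straining is analysed.

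A spurious risk ratio follows only if straining enters the model, and its size and direction are not fixed by the documents. Under the assumed 10% prevalence it lies between about 0.5 and 1.9 for the codings with unequal numbers of questionnaires, near 1 when the numbers are equal, and far above 1 under the literal reading. Prevalence, correlation and hernia timing are all assumptions. Only the complete separation under the literal reading, where every exposed man is a case, does not depend on them. That the sign turns on an unwritten coding choice is reason enough to settle the variable before analysis.

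The primary endpoint is untouched. The surgical contrast could be affected only indirectly, through adjustment, and by an unknown amount.

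**What to change.** 1. Delete the hernia-linked sentences under Questionnaire 12 months (Q 235) and Questionnaire 24 months (Q 256).
2. State in the numbered risk-factor list, in Covariates, stratum and subgroups, and in Statistical method whether straining is a candidate risk factor. Leaving it out would agree with those three sections as they stand and needs no new analysis.
3. If it is a candidate, define it identically for all men without reference to hernia status, using the preoperative item (Q 146). When doing so, check the item number: the preoperative list names urinary flow as Q149, while the straining item shown is Q 146.
4. If postoperative straining is of interest, add a secondary landmark analysis. Exposure is the three-month item (Q 221), outcome is a hernia first reported at the 12- or 24-month wave, and the rule is the same for cases and non-cases.

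Steps 1 to 3 change SAP wording only, since the data are already collected. The landmark analysis loses hernias found by three months. The hernia-contact items are listed as yes/no without a date, so timing for undated reports is known only by wave.

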### **Questionnaire 24 months**

*Q 23: Har ditt arbete varit kroppsligt aktivt den senaste månaden? With a 6 point Likert scale (0=Inte aktuellt jag jobbar inte, 1= nej inte kroppsligt aktivt alls, 2=ja, lite kroppsligt aktivt, 3=Ja måttligt kroppsligt aktivt, 4= Ja, mycket kroppsligt aktivt, 5= annat) The answers will be dichotomized with a cut-off point between 2 and 3 prior to analysis.*

*Q 230: Hur ofta har Du varit fysiskt aktivt i 30 minuter eller mer den senaste månaden..? With a 4 point Likert scale (1= aldrig, 2=ibland (1-2 ggr/v), 3=Ofta (3-4 ggr/v), 4= Dagligen eller nästan dagligen (5-7 ggr/vecka)) The answers will be dichotomized with a cut-off point between 2 and 3 prior to analysis.*

*Q 256: Hur ofta har Du varit tvungen att trycka på eller krysta för att börja kissa den senaste månaden? With a 6 point Likert scale (1=aldrig, 2=färre än 1 av 5 vattenkastningar, 3=färre än hälften av vattenkastningar, 4= ungefär hälften av vattenkastningar, 5= fler än hälften av vattenkastningar, 6=alltid). The answers will be dichotomized with a cut-off point between 3 and 4 prior to analysis. Interpreted as risk factor if answered "yes" on same or previous questionnaire as inguinal hernia is identified. Interpreted as risk factor and included in analyses if answered "yes" on same or previous questionnaire as inguinal hernia is identified*

### **CRF preoperatively**

Item 6, clinical stage (cT1-T4)

Item 8, ASA-classification

Item 9, PSA

Item 20, biopsy Gleason score

### **CRF perioperatively**

Item 1-2, Age at surgery

Item 17 Type of surgery

Item 18-23 Other procedures during prostate surgery

## ***Covariates, stratum and subgroups***

No additional variables apart from the variables that will be evaluated for risk factors will be included as covariates in the statistical model.

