## INTRODUCTION

The LAPPRO trial, a prospective, controlled non-randomized trial where robot assisted laparoscopic prostatectomy was compared with open retropubic prostatectomy, is the context for the described study, a secondary outcome of the trial. Inclusion took place during September 2008 until November 2011, with a total of 4003 included patients at 14 Swedish Departments of urology.

Since the middle of 1990s several studies have reported an increased risk for developing an inguinal hernia after prostatectomy [1-6] compared with the normal population. Patients operated with open radical retropubic prostatectomy (RRP) or robot assisted prostatectomy (RALP), had a threefold increased risk of being operated because of inguinal hernia [7]. Hence, evidence suggests an increased incidence of inguinal hernia even after minimal invasive surgery such as RALP[8]. But as some studies suggest the risk to be less with RALP compared to RRP[7] this study of a very large cohort of men operated by either retropubic or robot assisted laparoscopic prostatectomy will shed further light on this question.

The primary aim of this study is to assess the difference in risk of developing an inguinal hernia within 2 years of a prostatectomy comparing the techniques of RRP and RALP.

This statistical analysis plan was completed and finalized before the personnel involved in the project started the analyses of data.

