## ANALYSIS POPULATION, TYPE OF ANALYSIS

### *Analysis population*

The entire cohort in the LAPPRO trial (n=3706), where RALP was compared with RRP. Since it is a non-randomized study patient will be analysed as-treated.

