#### **Sample size**

The LAPPRO study was designed with the aim to compare RALP and RRP with regard to incontinence at 12 months [9]. Groin hernia formation is a secondary outcome in that study and hence sample size is not calculated for groin hernia formation.

In a previous study[7] the incidence of inguinal hernia operation within two years after prostatectomy was approximately 6% and 7.5% for RALP and RRP (a risk ratio of 0.80), respectively. With 3706 evaluable patients (2764 and 942 with RALP and RRP, respectively) and a true incidence of 6% and 7.5%, these will be detected with approximately 35% power. However, for the endpoint used here, the incidence is expected to be higher. As illustration, with true incidences of 10% and 12.5%, respectively, a difference will be detected with 55% power using a two-sided test at 5% significance level.

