#### **Statistical method**

The primary objective of evaluating the association between hernia incidence and operation and the evaluation of risk factor will be done simultaneously with the same statistical model. The relative risk of at least one inguinal hernia within 24 months after surgery, comparing surgical methods (RALP, RRP), will be modelled using a modified Poisson regression approach of Zou ([10]).

Except for the exposure, the surgical method (RALP, RRP), possible risk factors (age, physical workload, BMI, diabetes, pulmonary disease, smoking, hernia prior operation, physical activity and tumour size) will be evaluated by the same algorithm introduced by Bursac ("Purposeful selection of variables in logistic regression", Source Code for Biology and Medicine 2008;17). This model might also include interactions.

The key secondary objective will evaluate the same risk factors, but will include Lymph node dissection (yes/no) in the model.

The secondary objectives will be evaluated in an analogous way, using the risk factors ....

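### The primary RALP versus RRP model makes no provision for the 14 departments, so its interval may be too narrow if technique varies mainly between departments

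*SAP*

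**What the plan says.** The Introduction describes a controlled, non-randomised comparison and reports recruitment "with a total of 4003 included patients at 14 Swedish Departments of urology". Under Analysis population, the data set is "The entire cohort in the LAPPRO trial (n=3706), where RALP was compared with RRP", analysed as treated.

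Under Statistical method, the relative risk for surgical method "will be modelled using a modified Poisson regression approach". The candidate covariates are nine patient-level factors, chosen by a purposeful-selection algorithm. Neither department nor surgeon is among them.

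The section Covariates, stratum and subgroups consists of one sentence: "No additional variables apart from the variables that will be evaluated for risk factors will be included as covariates in the statistical model". It names no stratum. Nowhere does the SAP name department as a covariate, stratum, random effect or unit for the robust variance.

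The Sample size section uses 2764 RALP and 942 RRP patients. For 6% versus 7.5% it says "these will be detected with approximately 35% power". For the illustration "with true incidences of 10% and 12.5%, respectively", it says "a difference will be detected with 55% power using a two-sided test at 5% significance level".

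**The concern.** Men treated in the same department share surgeons, referral patterns, thresholds for repairing a hernia, and completeness of forms. The last matters here because the endpoint is built from physician reports and patient questionnaires, and a missing value counts as no hernia. A department that returns fewer forms will therefore appear to have fewer hernias.

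Nothing in the design balances technique across departments. To the extent that technique goes with department, outcomes within a technique group are correlated in a way that bears directly on the RALP versus RRP contrast. The robust variance of the modified Poisson approach corrects for fitting a Poisson model to a binary outcome. It allows for correlation within departments only if it is clustered on department, and the SAP does not say that it will be.

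At stake is the confidence interval for the primary comparison: chance variation between departments could be read as evidence of a difference between techniques.

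**Working it through.** **Inputs from the SAP.** n = 2764 (RALP) and 942 (RRP), total 3706; rates 6% v 7.5% and 10% v 12.5%; two-sided 5%; 14 departments.

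**Assumptions not in the SAP.** ICC of 0.002 to 0.01; all 14 departments contribute to the 3706 (the SAP ties them to the 4003 included); equal department sizes; technique set wholly by department (worst case).

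**Step 1: reproduce the stated power.** Two-proportion test with continuity correction, independent patients:

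power = Φ[(|d| − c − 1.96·SE₀)/SE₁], with c = ½(1/2764 + 1/942) = 0.00071, SE₀ the pooled and SE₁ the unpooled standard error.

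- 6% v 7.5%: SE₀ = 0.00922, SE₁ = 0.00970; (0.015 − 0.00071 − 1.96 × 0.00922)/0.00970 = −0.39, power 34.8% (stated: about 35%).
- 10% v 12.5%: SE₀ = 0.01163, SE₁ = 0.01219; (0.025 − 0.00071 − 1.96 × 0.01163)/0.01219 = 0.12, power 54.9% (stated: 55%).

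Both figures come out with no design effect, so they contain no allowance for clustering.

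**Step 2: baseline for the clustered figures.** The same formula without continuity correction (pooled formula) gives 37.6% and 57.2%. The clustered powers below must be compared with these, not with 35% and 55%.

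**Step 3: design effect.** m = 3706/14 = 264.7 and DE = 1 + (m − 1) × ICC. True type I error of a nominal 5% test that ignores clustering is 2[1 − Φ(1.96/√DE)]. Power comes from the pooled formula with n divided by DE.

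| ICC (assumed) | DE | SE too small by factor | 3706/DE | Type I error | Power 6% v 7.5% | Power 10% v 12.5% |
|---|---|---|---|---|---|---|
| 0 | 1 | 1 | 3706 | 5% | 38% | 57% |
| 0.002 | 1.53 | 1.24 | 2426 | 11% | 27% | 42% |
| 0.005 | 2.32 | 1.52 | 1598 | 20% | 20% | 30% |
| 0.01 | 3.64 | 1.91 | 1019 | 30% | 15% | 21% |

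**Step 4: check by simulation.** Beta-binomial departments, no true difference (10.5% in both groups), 20,000 runs, patient-level variance of the log relative risk.

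- Seven departments per technique: rejection rate 16% at ICC 0.005 and 26% at 0.01 (7% at 0.001).
- Same technique mix in all 14 departments: 4.9% and 4.8% (5.0% at 0.001).

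The first set is below the table because cluster sizes differ by arm: about 394 men per RALP department and 134 per RRP department. The smaller RRP arm carries 0.746 of the variance, from (1/942)/(1/942 + 1/2764). At ICC 0.005 the combined design effect is 0.254 × (1 + 393 × 0.005) + 0.746 × (1 + 133 × 0.005) = 2.0. This gives 2[1 − Φ(1.96/1.41)] ≈ 16%, in agreement with the simulation.

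**The case against.** The strongest objection is that the harm depends on facts that the SAP does not contain. If every department performed both techniques in the same proportion, the simulation shows no inflation. This stands: a reader might infer that the planned intervals are certainly too narrow, but the document supports only a conditional statement.

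Four other strong readings also go too far.

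- *That the covariate rule forbids the remedy.* The sentence restricts covariates and is silent on variance estimation. It bars a department term but not a clustered variance. That the variance would be patient-level is inferred from the default of the named method; the SAP does not state it.
- *That the comparison rests on something near 14 observations.* In the table the effective sample is about 1000 to 2400. The number of departments limits the degrees of freedom; it is not the effective sample size.
- *That 35% and 55% are upper bounds.* The SAP expects a higher incidence for its endpoint than in the earlier study. At the same risk ratio, 15% v 18.75% gives about 75% by the Step 1 formula: (0.0375 − 0.00071 − 1.96 × 0.01381)/0.01442 = 0.67. The stated figures assume independence at given rates and bound nothing.
- *That clustering would stop a department effect being reported as a technique effect.* It corrects the interval only. Systematic differences between departments stay in the relative risk.

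It is also fair to say that the power statement has little consequence: the SAP says that the sample was not sized for hernia, and the cohort is fixed.

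What survives is the omission itself. The plan provides no safeguard in the case where one is needed, and nothing in it shows that the harmless case applies.

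**Conclusion.** The point holds in conditional form. The SAP names no clustering unit and closes the covariate list without department, in a non-randomised comparison across 14 departments. If technique varies mainly between departments, the primary standard error is too small. In the worst case, at assumed ICCs of 0.002 to 0.01, it is too small by a factor of about 1.2 to 1.9. A nominal 5% test then rejects a true null about 11% to 30% of the time by the design-effect formula; at ICCs of 0.005 and 0.01 the simulation gives 16% and 26%, against 20% and 30% by the formula. If technique was mixed equally everywhere, the effect is about nil. The truth lies somewhere in that range, and the SAP does not allow it to be located. The stated power figures are arithmetically sound for independent patients. The change is worth making because it is cheap and bears on the primary interval.

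**What to change.** - **Statistical method.** Keep the modified Poisson model. State that its sandwich variance is clustered on department, with a small-sample correction and a t reference because there are only 14 clusters. Compute it within each imputed data set before pooling. State also that where technique is set by department, clustering widens the interval but cannot separate a department effect from a technique effect.
- **Covariates, stratum and subgroups.** Amend the sentence so that, where departments performed both techniques, a department-stratified estimate is reported as a sensitivity analysis.
- **Sample size.** Add that the 35% and 55% assume independent patients at the given rates.

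**Cost.** Some SAP wording, a department identifier in the analysis data set, and modest programming, since the corrected variance must run alongside the multiple imputation and the variable selection. The statistical price is wider intervals.

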## **Possible risk factors for incisional hernia ?**

Age above 70

Artherosclerosis

BMI above 30

Hypertension

Previous abdominal surgery

Smoking

Diabetes

Pulmonary disease

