## STATISTICAL METHODOLOGY

### *General principles*

#### **Multiplicity**

#### **Interpretation of results**

A risk factor is here referred to as a variable that is associated with the outcome of interest. The variables specified in the previous sections are, based on clinical judgement and earlier studies, regarded as potentially clinically relevant. Interpretation of the results will consider clinical relevance of the estimated degree of association and will be cautiously addressed due to the risk of spurious and false positive associations.

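### The RALP vs RRP relative risk could keep residual confounding, because its closed covariate list was chosen as hernia risk factors and shuts out measured baseline variables

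*SAP*

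**What the plan says.** Under Analysis population, the SAP takes the whole cohort and states: "Since it is a non-randomized study patient will be analysed as-treated". Under Statistical method, a single modified Poisson model serves both the RALP vs RRP relative risk and the evaluation of risk factors. Besides surgical method, its candidates are "possible risk factors (age, physical workload, BMI, diabetes, pulmonary disease, smoking, hernia prior operation, physical activity and tumour size", and a purposeful-selection algorithm works on them. The numbered list under Variables and Endpoints has the same nine entries, with tumour risk category in place of tumour size.

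The section Covariates, stratum and subgroups closes the list: "No additional variables apart from the variables that will be evaluated for risk factors will be included as covariates in the statistical model". Interpretation of results defines a risk factor as a variable associated with the outcome and says that the specified variables are "based on clinical judgement and earlier studies, regarded as potentially clinically relevant".

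Other baseline data are extracted for the same analysis. The preoperative questionnaire supplies "Sociodemographics (Q4-6), BMI (Q8-9), relevant comorbidities (Q30, 35, 41, 43, 44), previous abdominal surgery (Q52), previous IH surgery (Q46, 47". The preoperative CRF supplies "Item 8, ASA-classification". The risk-factor list for incisional hernia, a different outcome, includes "Previous abdominal surgery".

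**The concern.** Technique was not assigned at random, so a pre-treatment variable related both to the technique used and to the recorded outcome distorts the relative risk unless it is adjusted for. The SAP describes no propensity score, matching, stratification or sensitivity analysis with a wider adjustment set. The covariate list therefore carries the whole task, yet it was assembled to answer another question: which variables predict hernia. Predictors of the choice of technique are not considered.

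The three excluded items are plausible confounders, although the SAP documents no such link. Earlier abdominal surgery and general fitness may influence whether an open or a laparoscopic operation is done. Sociodemographic factors may relate to where a man is operated on, among 14 departments, and to whether he seeks care. A patient's report of seeking care for a suspected hernia counts as an event, and missing values count as no hernia, so such factors could move the measured outcome.

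The planning effect is modest (risk ratio 0.80), so even a small distortion could matter relative to it.

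**Working it through.** **1. What can enter the model**

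| Baseline item | Extracted | Among the nine candidates |
|---|---|---|
| Previous abdominal surgery (Q52) | Yes, preoperative questionnaire | No; listed for incisional hernia only |
| ASA class (Item 8) | Yes, preoperative CRF | No; diabetes and pulmonary disease are |
| Sociodemographics (Q4-6) | Yes, preoperative questionnaire | Only age, itself taken from the perioperative CRF |

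The key secondary model adds lymph node dissection and nothing from this table. The variables planned under Demography and patient characteristics also omit the three items apart from age, so the planned baseline table would not show an imbalance in them.

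**2. The plan's own figures**

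Inputs from Sample size: 2764 RALP, 942 RRP, two-sided 5%; incidences 6% vs 7.5% (stated power about 35%) and 10% vs 12.5% (stated power 55%). A continuity-corrected test of two proportions gives 34.8% and 54.9%. Other standard forms give 34.0% and 53.6% (unpooled), 35.5% and 55.6% (arcsine), and 37.6% and 57.2% (pooled). The stated power reproduces. It does not bear on the covariate rule, but it confirms the inputs used below.

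Expected events:
- 0.06 × 2764 + 0.075 × 942 = 165.8 + 70.7 = about 236
- 0.10 × 2764 + 0.125 × 942 = 276.4 + 117.8 = about 394

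Standard error of the log relative risk at 10% vs 12.5%: √(0.90/276.4 + 0.875/117.75) = 0.103.

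**3. Possible size of the bias (assumed inputs)**

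For one omitted binary factor with hernia risk ratio RRc, the same in both groups, and prevalences pRALP and pRRP, the relative risk is multiplied by

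B = [1 + pRALP(RRc − 1)] / [1 + pRRP(RRc − 1)].

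The prevalences and RRc are assumptions; none is in the SAP. The share of the planned effect is ln B / ln 0.80, with ln 0.80 = −0.223. The two-sided error rate when technique has no effect is Φ(−1.96 + |ln B|/0.103) + Φ(−1.96 − |ln B|/0.103).

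| pRALP | pRRP | RRc | B | Share of ln 0.80 | Error rate |
|---|---|---|---|---|---|
| 20% | 20% | any | 1.00 | 0% | 5.0% |
| 20% | 25% | 1.3 | 1.06/1.075 = 0.986 | 6% | 5.2% |
| 20% | 30% | 1.5 | 1.10/1.15 = 0.957 | 20% | 7.1% |
| 20% | 35% | 1.5 | 1.10/1.175 = 0.936 | 30% | 9.8% |
| 35% | 20% | 1.5 | 1.175/1.10 = 1.068 | 30%, opposite direction | 9.8% |

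A true relative risk of 0.80 would be seen as 0.80 × 0.936 = 0.75 in the fourth row and as 0.80 × 1.068 = 0.85 in the last.

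These are crude figures for one factor. What matters is the part left after the variables already in the model. For ASA class that part is probably smaller, because it overlaps diabetes and pulmonary disease. Several omitted factors could add up or cancel.

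**The case against.** The strongest reply is that collecting a baseline variable does not oblige a plan to adjust for it. A confounder must relate to both technique and inguinal hernia, and the SAP shows neither link for any of the three items. Previous abdominal surgery appears only for incisional hernia, which may mean that the authors considered it and assigned it to that outcome. The nine candidates rest on clinical judgement and earlier studies that cannot be examined here. All of this stands. A reader might infer that the relative risk is confounded, or that it is biased in favour of RALP. The documents support neither inference, since no bias and reversed bias are equally open.

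A reader might also infer that adding the variables to the existing model costs nothing. It does not. Technique and risk factors share one model, and ASA class summarises comorbidity. Forcing it in would change the meaning of the diabetes and pulmonary-disease coefficients, which serve the secondary objective. The SAP also does not say what Q4-6 contain, so coding must be settled first.

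Two further limits stand. PSA and biopsy Gleason score are extracted and left out in the same way, so the three items are not claimed to complete the confounder set. And the closure is not perfectly worded: the heading above the questionnaire items mentions risk factors in general, and straining to urinate is to be included in analyses although it is in neither inguinal list. Even so, the explicit model list under Statistical method contains none of the three items.

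The objection does not answer why a list built to predict hernia should also serve, closed and without justification, as the adjustment set for a non-randomised comparison of techniques.

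**Conclusion.** The point holds as one of possible residual confounding. The SAP fixes an adjustment set chosen as hernia risk factors and bars measured pre-treatment variables from the RALP vs RRP model without giving a reason. Whether this biases the estimate, how much and in which direction cannot be determined from the SAP. On the assumptions above the multiplier runs from 1.00 to about 0.94, up to 30% of the planned log effect, and exceeds 1 if the imbalance is reversed (1.07 in the mirror case). These figures show what modest imbalances could do; they do not estimate what happened in this cohort.

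**What to change.** Amend Covariates, stratum and subgroups and Statistical method so that the technique effect is also estimated in a separate, prespecified modified Poisson model. That model should force in previous abdominal surgery (Q52), ASA class (Item 8) and the Q4-6 items, together with all nine listed factors. State the coding of each added variable, including what Q4-6 are, and impute missing values in the same MICE run. Keep the existing model unchanged for the risk-factor objective, so that its diabetes and pulmonary-disease coefficients keep their meaning. Report the RALP vs RRP relative risk from both models side by side.

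The cost is one extra model, a few coding rules, a few degrees of freedom against about 236 to 394 expected events, and some overlap of ASA class with the listed comorbidities. No new data collection is needed.
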